### Participants

Patients were recruited from Northern Alberta Renal Program (NARP) clinics at Alberta Health Services (AHS) in Edmonton, Alberta between November 2011 and December 2013. This is a multidisciplinary program (endocrinologists, nephrologists, registered nurses (RN), registered dietitians (RD), pharmacists and social workers) that provides care to over 1,500 patients with diabetic nephropathy in northern Alberta. Sixty adults with diabetes and nephropathy per vitamin D_3_ supplementation group were recruited into this study (n = 120 total). Potential participants were approached by a member of the clinical team (e.g. RD or RN) and asked if a research team member could discuss this study with them. If verbal consent was provided, then a research team member contacted the patient, explained the study to them and determined their eligibility for participation in this RCT; if eligible and agreed by the patient, informed consent was signed and the baseline study appointment was booked. Subsequent study visits (e.g. 3 month and 6 month follow-up appointments) were booked via telephone calls made approximately 2 months later to follow-up with the participants and address any questions or concerns they may have had about their supplement strategy. Patient eligibility for this RCT was determined upon information available in the medical chart at time of screening. Inclusion/exclusion criteria are as follows:

### Inclusion criteria

1) Adult (18–80 years) patients diagnosed with diabetes (Type 1 and Type 2) and stage 1–4 CKD (Glomerular Filtration Rate (GFR) 15–89 mL/min/1.73 m^2^) [34].

### Exclusion criteria

1) Patients with co-morbid conditions known to affect vitamin D metabolism including gastrointestinal, liver, rheumatoid or bone disorders (e.g. hyperthyroidism, untreated celiac disease, cancer, Paget’s disease, sarcoidosis, malabsorption, etc.). Individuals with severe, permanent vision impairment will be excluded as this will preclude them from reading supplement labels accurately and safely. Pregnant women will be excluded as Dual-energy X-ray Absorptiometry (DXA) scans are not recommended during pregnancy. Patients weighing >136 kg will be excluded as the DXA table cannot accommodate this weight.

2) Patients on drug therapy known to interfere with vitamin D (e.g. oral glucocorticoids, cholestyramine, colestipol, mineral oil, Orlistat, digoxin).

3) Patients on other forms of active D metabolites (e.g. calcitriol, vitamin D2).

4) Patients with stage 5 CKD (GFR <15 mL/min/1.73 m^2^), receiving dialysis or on a kidney transplant list.

5) Patients with pre-existing hypercalcemia (>2.75 mmol/L), hyperphosphatemia (>2.0 mmol/L), severe secondary hyperparathyroidism (PTH >66 pmol/L), and serum 25(OH)D >200 nmol/L.

6) Patients with serum 25(OH)D <37.5 nmol/L at time of screening to control for correction of vitamin D deficiency [5].

7) Patients undergoing strict heavy exercise for weight control and/or those who used sunscreen lotion on a regular basis.

### Sample size

This sample size (n = 120) was based on the ability to detect a mean difference of 25–50 nmol/L in serum 25(OH)D from baseline levels after 6 months of vitamin D_3_ supplementation in each group (α = 0.05 and β = 0.8) with an additional 15% to account for potential subject attrition [5,8]. Recent evidence has shown that a mean increase of 25 nmol/L in 25(OH)D with 1,000 IU/day supplemental vitamin D_3_ was insufficient to promote 25(OH)D in excess of 100 nmol/L – the level of 25(OH)D that has been associated with having a beneficial impact on markers of bone health [5,7,23]. Therefore, we chose this specific vitamin D_3_ dose to ensure serum 25(OH)D would increase by 25–50 nmol/L.

### Data collection

Assessment of vitamin D status, bone health and lifestyle factors (diet, physical activity, sunlight exposure, QoL) were performed during study visits at the Clinical Research Unit (CRU) at the University of Alberta at baseline, 3 and 6 months post study enrolment between January 2012 and June 2014. Participants were given a 3 month supply of their respective vitamin D_3_ supplementation strategy at baseline and again at the 3 month study visit. They were asked to return their vitamin D_3_ vials/pill containers to the study investigators at the 3 and 6 month study visits. At baseline, information related to patient demographics and anthropometrics was collected. This included age, gender, ethnicity, medications/supplement use, insulin regimen, height, weight (Health O-Meter Professional model 597KL, Pelstar LLC, Alsip, IL, USA) and BMI. Changes in these variables between appointments were documented (e.g. medications, height, weight). Bone mineral density (BMD) was measured at baseline using Dual-energy X-ray Absorptiometry (DXA); a validated tool to assess BMD (General Electric LUNAR Prodigy, version 10.5, Madison, WI, USA). Whole body scans as well as site specific scans of the lumbar spine (L1-L4) and left total hip (including femoral neck) were conducted. The precision error, expressed as a percentage coefficient of variation (%CV), for the Lunar DXA located in the CRU are as follows: whole body BMD 0.7%, lumbar spine 0.9% and total hip 1.2%.

Lifestyle factors were assessed at baseline, 3 and 6 months using validated tools [35-41]. These include: 1) 3-day food record to assess vitamin D and calcium intake and other dietary factors known to influence vitamin D and bone health (phosphorus, carbohydrates, protein, caffeine). Dietary intake was analyzed using the Food Processor Database (Food Processor SQL, v.10.8, ESHA Research, Salem, Oregon, USA); 2) Weight-bearing physical activity records; 3) Sunlight exposure questionnaires; 4) Health related QoL (SF-36) questionnaires (http://www.qualitymetric.com Liscence Number QM019185 OPTUMInsight^TDM^); and 5) Adherence and acceptance surveys [34-38,42-44]. Adherence to vitamin D_3_ supplementation was also assessed by pill counts of returned vitamin bottles at 3 and 6 months.

### Laboratory investigations

To avoid risk of hypoglycemic events due to variations in appointment availability (e.g. insulin regimen incompatibility with fasting and later appointment times), random serum/plasma samples for measurement of routine clinical blood work and study blood work were collected. However, most blood samples were collected between 10 am-2 pm; approximately 2 hours post meal consumption (of either breakfast or lunch) to minimize the potential influences of variable blood collection times on bone turnover marker expression [39].

Blood samples were collected onsite at each research visit by a trained phlebotomist using validated techniques and tubes (SST gel for serum, and lithium heparin PST gel and EDTA plasma). Once collected, blood samples were immediately held at 2-8°C until processing by the research team or provincial laboratory system. Patients routinely receive clinical blood work to assess their glycemic control, kidney function and overall health, including: estimated GFR (eGFR), fasting/random blood glucose (FBG/RBG), urea, creatinine, hemoglobin A1c (HbA1c), calcium, albumin, phosphorus, magnesium, 25(OH)D and PTH. These variables were collected at all 3 study visits (except PTH) along with 1,25(OH)_2_D status. Serum PTH, bone turnover markers and fibroblast growth factor-23 (FGF-23) were collected at baseline and 6 month follow-up study visits.

Routine clinical blood work, 1,25(OH)_2_D and PTH were measured by validated, specific and sensitive methodologies used by the provincial laboratory system. Estimated GFR was calculated using a validated online equation provided by K/DOQI (Modification of Diet in Renal Disease (MDRD) study group and the Chronic Kidney Disease Epidemiology Collaboration (CKD-EPI) group; http://www.kidney.org/professionals/kdoqi/gfr_calculator.cfm). Bone turnover markers were analyzed by the research team using standardized commercial ELISA kits. After blood collection, EDTA plasma and serum clot samples (e.g. SST gel) were kept for approximately 30–60 minutes at 2-8°C and then centrifuged at 2,500 RPM at 4°C for 10 minutes (CR4.22 centrifuge, Jouan, Winchester, VA, USA). Recovered serum and plasma were aliquoted into clean micro-tubes according to volumes required for each specific assay to be tested in duplicate. Samples were stored frozen at −80°C until ELISA testing, and prepared according to the manufacturer instructions for each commercial ELISA kit: serum intact osteocalcin (OC; MicroVue Osteocalcin EIA Kit, Quidel, San Diego, CA, USA), serum bone-specific alkaline phosphatase (BAP; MicroVue BAP EIA Kit, Quidel, San Diego, CA, USA), serum N-telopeptide of type 1 collagen (NTx; Osteomark NTx Serum, Wampole Laboratories, Princeton, NJ, USA), and plasma intact fibroblast growth factor-23 (FGF-23; Human Intact FGF-23 ELISA Kit, Immunotopics Inc, San Clemente, CA, USA). The intra-assay (a) and inter-assay (b) coefficient of variance (CV) for these commercial kits are as follows: OC a) 4.8-10.0%, b) 4.8-9.8%; BAP a) 3.9-5.8%, b) 5.0-7.6%; NTx a) 4.6-13.99%, b) 6.9-13.99%; and FGF-23 a) 2.6-4.4%, b) 6.1-6.5%.

### Outcome measurements

Outcome measurements are illustrated in Figure 1.

**Figure 1 F1:**
[figure not shown]
**Study design**^**1**^**. **^1^Abbreviations: Northern Alberta Renal Program (NARP); Alberta Health Services (AHS); randomized controlled trial (RCT); micrograms (mcg); Body mass index (BMI); Dual X-ray absorptiometry (DXA); Bone mineral density (BMD); Hemoglobin A1c (HbA1c); random blood glucose (RBG); estimated glomerular filtration rate (eGFR); 25-hydroxy vitamin D (25(OH)D); 1,25-dihydroxy vitamin D (1,25(OH)_2_D); alkaline phosphatase (ALP); osteocalcin (OC); bone-specific alkaline phosphatase (BAP); N-telopeptide of type 1 collagen (NTx); fibroblast growth factor-23 (FGF-23).

### Primary outcome variables

#### Serum 25(OH)D and 1,25(OH)_2_D

Serum 25(OH)D is considered the most reliable measure of vitamin D status as it accounts for cutaneous and dietary sources of vitamin D [40].

A mean increase in serum 25(OH)D of 25–50 nmol/L was chosen as a conservative target for 25(OH)D as 1,000 IU/d has been shown to increase serum 25(OH)D by 25 nmol/L in renal patients [5]. 1,25(OH)_2_D was measured to determine concentration of active vitamin D in participants and explore the relationship of active vitamin D with 25(OH)D levels and with bone health. Vitamin D levels were measured by validated, specific and sensitive methodologies used by the provincial laboratory system. The ratio of 1,25(OH)_2_D (product) to 25(OH)D (precursor) was calculated as a surrogate measure of 1α-hydroxylase activity (product to precursor ratio).

### Bone health

Bone health was assessed by measurement of BMD and plasma/serum levels of bone turnover markers. BMD was measured using DXA (non-invasive gold standard) to characterize bone health of participants at time of study entry. Bone turnover markers were measured at baseline and at 6 months; bone resorption: N-telopeptide type 1 collagen (NTx); and bone formation: bone-specific alkaline phosphatase (BAP) and osteocalcin (OC) [34]. Serum PTH and fibroblast growth factor-23 (FGF-23; measure of bone-kidney axis) were measured at baseline and 6 months to assess how serum PTH/FGF-23 concentrations change with our vitamin D supplementation strategies.

### Secondary outcome variables

#### Participant acceptance and adherence survey

Participants completed a validated survey developed to assess adherence to drug therapy in adults with chronic disease (e.g. hypertension) that has been adapted for our specific therapy [37]. This survey consists of open and close-ended questions. This was used to assess and compare adherence to the two different dosing strategies, and consider participants’ preferences and perceptions of their supplementation strategy. Adherence to the dosing regimens was also assessed by pill counts (at 3 and 6 month visits).

### Health-related QoL questionnaire (SF-36)

Participants completed the SF-36 QoL questionnaire (a common and validated tool used to asses QoL in chronic disease) at baseline and 6 months after study entry [38]. This questionnaire considers parameters of the participants’ functional capacity, social, and emotional well-being and was used to compare QoL pre-and-post intervention. (Liscence Number QM019185 OPTUMInsight ^TDM^).

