### Objectives

1. Examine the impact of two approaches to high dose, oral, vitamin D_3_ supplementation (2,000 IU/d vs. 40,000 IU/m) for 6 months on overall vitamin D status (25(OH)D and 1,25(OH)_2_D) and markers of bone turnover (bone-specific alkaline phosphatase, osteocalcin, N-telopeptide of type 1 collagen) in adult patients with diabetic nephropathy.

2. Examine daily vs. monthly vitamin D_3_ supplementation strategies in regards to adherence, patient satisfaction and quality of life in adult patients with diabetic nephropathy.

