### Hypotheses

1. Vitamin D_3_ supplementation (2,000 IU/d vs. 40,000 IU/m) for 6 months will result in significantly improved overall vitamin D status and improved markers of bone health in adult patients with diabetic nephropathy. Serum 25(OH)D will increase by a minimum of 25–50 nmol/L post-supplementation. Markers of bone resorption will decrease and markers of bone formation will increase after 6 months of vitamin D_3_ supplementation when compared to baseline levels.

2. Monthly dosing of vitamin D_3_ (40,000 IU/m) over 6 months will result in improved patient adherence and satisfaction with vitamin D_3_ supplementation when compared to daily dosing of vitamin D_3_ (2,000 IU/d) resulting in improved overall vitamin D status, bone health parameters, and quality of life.

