### Statistical analysis

Data analysis was performed on an intention-to treat basis as well as a per-protocol basis. Analyses were performed using Microsoft Excel 2010 and Statistical Analysis Software (SAS; version 9.3 SAS Institute, Cary, NC, USA). Statistical significance was determined at p < 0.05. Continuous variables were expressed as mean, median, ranges, and standard error (SE) or standard deviation (SD). The differences between dosing type (daily vs. monthly) over the intervention period were assessed by repeated measures analysis of variance, followed by a post-hoc pair-wise t-test with Bonferroni corrections to assess for within and between group comparisons. Potential risk factors for the development of vitamin D insufficiency (serum 25(OH)D <75 nmol/L) and poor bone health (T-scores < −2 SD) in adults with diabetic nephropathy include bone turnover, vitamin D intake, vitamin D status (serum levels of 25(OH)D and 1,25(OH)_2_D), age, gender, ethnicity, severity of kidney disease, diabetic management/control, exposure to sunlight, level of activity, and psychosocial and lifestyle factors.

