Continuous and categorical variables (e.g. 25(OH)D, lab parameters, BMD T-scores, adherence scores) were quantitatively analyzed, and open-ended questions regarding participants’ perceived facilitators and barriers were categorized into key themes. Bivariate and univariate analysis were done to assess the potential effect of these variables on vitamin D status and bone health (bone turnover markers).Variables shown to be associated with a poor vitamin D status were assessed using multivariate logistic regression models to determine risk for development of vitamin D deficiency and poor bone health. Regression analysis was also conducted to assess correlation between biochemical parameters (PTH, 25(OH)D, 1,25(OH)_2_D, calcium, phosphorus, magnesium, albumin, eGFR, RBG) and bone turnover markers. Analysis of variance was performed to assess for significant differences in vitamin D status and bone turnover markers over the intervention period in both groups. Regression analysis was performed with serum 25(OH)D and plasma PTH as categorical variables; e.g. 25(OH)D sorted by greater/less than 75 nmol/L and plasma PTH sorted by greater/less than 7.15 pmol/L, the optimal concentrations for bone health [5,26]. Where necessary, vitamin D was adjusted for potential confounding variables (e.g. age, gender, ethnicity, disease severity) using an analysis of co-variance. When adherence to daily vitamin D dosing regimen was greater or less than 69%, the variation in compliance was also accounted for in an analysis of co-variance. For variables demonstrating skewed distributions a logarithmic transformation was used to normalize the data.

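### The SF-36 paragraph names a pre-versus-post comparison, while Objective 2 asks about daily versus monthly dosing; the article should say which contrast answers it

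*Protocol article*

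**What the plan says.** Under Objectives, the second objective is to "Examine daily vs. monthly vitamin D_3_ supplementation strategies in regards to adherence, patient satisfaction and quality of life". Under Hypotheses, the second hypothesis predicts that monthly dosing will do better than daily dosing on adherence and satisfaction, "resulting in improved overall vitamin D status, bone health parameters, and quality of life". Both pose quality of life as a comparison of the two randomized strategies.

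The section on the SF-36 says that the questionnaire "was used to compare QoL pre-and-post intervention" and mentions no comparison by arm. The section just before it, on the acceptance and adherence survey, does name the arms: "This was used to assess and compare adherence to the two different dosing strategies".

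The Statistical analysis section states a general model: "The differences between dosing type (daily vs. monthly) over the intervention period were assessed by repeated measures analysis of variance", followed by Bonferroni-corrected pairwise t-tests "to assess for within and between group comparisons". It neither lists the outcomes covered nor limits them. A later sentence in the same section describes an analysis of variance for "significant differences in vitamin D status and bone turnover markers over the intervention period in both groups"; quality of life is not in that sentence.

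**The concern.** The outcome section and the objective point to different contrasts. A pre-post comparison asks whether scores moved over six months in the patients studied. Objective 2 asks whether they moved differently under monthly and daily dosing. The first does not answer the second: both arms can improve equally, and one arm can cross the significance threshold while the other just misses it, with no difference between the strategies.

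The general model does not settle the matter, because it licenses both kinds of test and does not say which one answers Objective 2. A report could follow the SF-36 section, give p-values for change in each arm, and present a significant gain on monthly dosing beside a non-significant one on daily dosing as support for Hypothesis 2. That would be consistent with the article's wording and would still be no evidence of an arm difference.

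**Working it through.** No figure in the article bears on this point, so there is nothing to reproduce. The check is a comparison of the text, followed by an illustration on assumed values.

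**1. The text side by side**

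- Objectives and Hypotheses: monthly versus daily, quality of life included.
- Acceptance and adherence survey: between strategies, stated outright.
- SF-36: pre versus post; no between-arm contrast named.
- Statistical analysis, general sentence: daily versus monthly over time; outcomes not listed; within- and between-group tests both allowed.
- Statistical analysis, later ANOVA sentence: vitamin D status and bone turnover markers only.

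With SF-36 scores at baseline and 6 months, the group-by-time term of the general model equals the between-arm difference in mean change. The model can therefore answer Objective 2, but nothing says that this term, rather than the within-arm tests, is the quality-of-life result.

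**2. What within-arm testing can show when the arms do not differ**

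Inputs from the article: 60 patients per arm (Study design); 15% attrition (Sample size), giving 60 × 0.85 = 51; significance at 0.05 (Statistical analysis), taken as two-sided. Assumption: both arms shift by the same s SD of change, with s from 0.2 to 0.5.

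The chance that a given arm's pre-post test is significant is p = Φ(s√n − 1.96). The chance that exactly one of two independent arms is significant is 2p(1 − p).

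| n per arm | s | p, given arm | exactly one arm |
|---|---|---|---|
| 60 | 0.2 | 0.34 | 0.45 |
| 60 | 0.3 | 0.64 | 0.46 |
| 60 | 0.5 | 0.97 | 0.05 |
| 51 | 0.2 | 0.30 | 0.42 |
| 51 | 0.3 | 0.57 | 0.49 |
| 51 | 0.5 | 0.95 | 0.10 |

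A direct between-arm test is significant with probability 0.05 in every row.

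In points, the row with n = 51 and s = 0.3 corresponds, for example, to an assumed 3-point shift with an SD of change of 10: 3/(10/√51) = 2.14 and Φ(2.14 − 1.96) = 0.57.

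**3. Effect of the planned Bonferroni correction**

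The table uses uncorrected tests. If the correction spans 2 to 4 comparisons (an assumption), the 0.57 falls to about 0.46 to 0.36. The chance of exactly one significant arm is then 2 × 0.46 × 0.54 = 0.50 to 2 × 0.36 × 0.64 = 0.46. In this example the correction lowers each arm's chance of significance but leaves the misleading pattern about as likely.

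**4. What the right contrast can detect**

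At 80% power and two-sided 0.05, the between-arm detectable difference is (1.96 + 0.84)√(2/n): 0.51 SD at 60 per arm and 0.55 SD at 51. The within-arm figure, (1.96 + 0.84)/√n, is 0.36 SD and 0.39 SD. The within-arm test reaches significance more easily, which makes it the tempting one to report.

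**The case against.** The strongest reply is that the statistical section already handles this. Its between-arm model is not restricted to certain outcomes, and the SF-36 section may only describe the instrument and its timing. Measuring before and after is what a repeated measures model needs, and the section does not say that pre-post is the only comparison. A condensed article may also leave the exact contrast for a secondary questionnaire to a fuller document that is not shown.

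Much of this stands. A reader might infer that Objective 2 has no planned analysis for quality of life; the general model rules that out. What remains is that the article does not leave the SF-36 contrast unstated. It names one that differs from its objective, directly after naming the between-strategy contrast for adherence, and the general model permits either.

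A reader might also blame the lack of an untreated arm or the open-label design. Neither supports the point. Daily versus monthly needs only the two randomized arms; an untreated group would matter only for crediting a pre-post change to supplementation itself. Knowledge of treatment can bias a self-reported score under either analysis, and the proposed change does not remove that.

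Finally, the 0.57 is the power to detect a within-arm shift that is real by assumption. It is not a false-positive rate. It misleads only if the result is then read as evidence on monthly versus daily dosing, and nothing in the article says that it will be.

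**Conclusion.** The inconsistency is real and limited. The SF-36 section names a contrast that cannot answer Objective 2, and the statistical section offers one that can without tying it to the SF-36 or ranking it above within-arm tests. The stronger conclusion, that quality of life cannot be compared between the arms under this plan, is not supported.

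The probability of 0.42 to 0.49 for exactly one significant arm rests on an assumed shared shift of 0.2 to 0.3 SD, independent arms, 51 to 60 patients per arm and uncorrected tests. At 0.5 SD it falls to 0.05 to 0.10, because both arms are then usually significant. The article gives no SF-36 SD or expected change, so these figures illustrate the risk and do not estimate it. Severity is minor to moderate: a secondary outcome, and no stated figure changes.

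**What to change.** Reconcile the SF-36 section with the Statistical analysis section:

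- In the SF-36 section, state that the comparison for Objective 2 is the between-arm difference (monthly minus daily) at 6 months, adjusted for the patient's baseline SF-36 score, with a 95% interval, and that within-arm change is descriptive only.
- In the Statistical analysis section, state whether the repeated measures model covers the SF-36 and which of its terms answers Objective 2.
- In the same edit, settle the SF-36 schedule. Data collection lists it at baseline, 3 and 6 months; the SF-36 section gives baseline and 6 months. This fixes the time points in the model.

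The group-by-time contrast of the existing model would also answer the question. Baseline adjustment is suggested because it uses the same data and is generally more precise: with equal SDs at both visits and correlation r between them, its variance is (1 + r)/2 times that of the change-score contrast, which is below 1 for any r below 1.

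The cost is a few sentences and no new data. If a fuller protocol or analysis plan already fixes this contrast, a reference to it is enough.
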